# Reducing malaria transmission in forest-going mobile and migrant populations in Lao PDR and Cambodia: protocol for stepped-wedge cluster-randomised controlled trial

**DOI:** 10.1186/s12879-022-07724-5

**Published:** 2022-09-24

**Keywords:** Malaria, Prevention, Vector, Migrant, Elimination, Vivax, Falciparum, Community-delivered intervention

## Abstract

**Background:**

Countries of the Greater Mekong Sub-region aim to achieve malaria elimination by 2030. In the region, malaria is concentrated in high-risk areas and populations such as forest-going mobile and migrant populations (MMPs). However, routine protective measures such as long-lasting insecticidal nets do not prevent all infectious bites in these high-risk populations. Evidence for the effectiveness of a personal protection package tailored to forest-going MMPs which is acceptable, feasible, and cost-effective for reducing malaria transmission is required to inform the malaria elimination toolkit in the region.

**Methods:**

A personal protection package consisting of long-lasting insecticidal hammock net, insect repellent and health communication pamphlet was developed in consultation with relevant implementing partners from Cambodia and Lao PDR. An open stepped-wedge cluster-randomised controlled trial will be conducted over a period of 12 months in a minimum of 488 villages (~ 428 in Lao PDR and ~ 60 in Cambodia) to evaluate the effectiveness of the personal protection package. Villages will be randomised into 11 blocks, with blocks transitioned in random order from control to intervention states at monthly intervals, following a 1-month baseline period. The primary outcome of the trial is the prevalence of *Plasmodium* spp. infection diagnosed by rapid diagnostic test. Difference in prevalence of malaria infection will be estimated across intervention and control periods using generalized linear mixed modelling. Nested within the stepped-wedge cluster-randomised controlled trial is a mixed-methods study to explore the acceptability of the personal protection package, feasibility of implementing a personal protection package as a vector control intervention, and knowledge, attitude and practice of MMPs regarding malaria prevention; and cost-analysis to determine the cost-effectiveness of implementing a personal protection package.

**Discussion:**

This study, using a rigorous design and mixed-methods methodology, will evaluate whether a personal protection package can reduce residual malaria transmission among forest-going MMPs in Cambodia and Lao PDR. It will also measure implementation research outcomes such as effectiveness of the intervention package, cost-effectiveness, acceptability, and feasibility, in order to inform potential national and regional policy.

*Trial registration* This trial was prospectively registered on ClinicalTrials.gov (NCT05117567) on 11th November 2021

**Supplementary Information:**

The online version contains supplementary material available at 10.1186/s12879-022-07724-5.

## Background

In the Asia–Pacific region, more than two billion people are at risk of malaria, a vector-borne disease caused by *Plasmodium* spp. parasites transmitted by *Anopheles* spp. mosquitoes [1]. The Greater Mekong Sub-region (GMS) is a region in the Asia–Pacific consisting of Cambodia, Lao People’s Democratic Republic (Lao PDR), Myanmar, Thailand, Viet Nam, and Yunnan Province of China. The GMS has achieved an 88% reduction in indigenous malaria cases between 2012 and 2020 [2], largely attributed to the scale-up of community-based case management services for malaria operated by volunteers [3]. In recent years, thousands of malaria volunteers have been recruited across the GMS, especially in rural areas where the coverage of formal health services is limited, to provide essential malaria services such as prevention, diagnosis and treatment of malaria cases and referral of severe malaria cases [3, 4]. These malaria volunteers will also have a key role in achieving malaria elimination goals—GMS countries have committed to malaria elimination by 2030 in order to combat the emergence of drug resistant malaria in the GMS [5].

However, there are several challenges impeding progress towards malaria elimination in the GMS. One of the main challenges is the considerable heterogeneity of malaria transmission in the region. In the GMS, malaria is highly concentrated in hard-to-reach areas along international borders, and in forests and forest fringe communities including forest-going mobile and migrant populations (MMPs) [6–9]. MMPs are at particular risk of malaria due to their challenges accessing formal malaria services due to their mobility and remoteness [10], as well as their propensity for working outside which exposes them to *Plasmodium* spp. infected mosquitos [4]. Targeting these high-risk areas and populations will be critical to achieve regional elimination goals [7]. However, the current, mainstream interventions for malaria prevention deployed by countries in the GMS—long-lasting insecticidal nets [11] together with focal responsive indoor residual spraying and larval source management as appropriate [12, 13]—do not prevent the majority of infective bites by the dominant vectors which prefer to bite and rest outdoors and during the day [14]. Therefore, personal protection may be more appropriate for reducing malaria, particularly in high-risk groups such as forest-going MMPs.

Few studies have examined the effectiveness of personal protection in reducing malaria in the region [15], particularly in the context of distribution within established malaria service distribution mechanisms such as malaria volunteer networks. A recent effectiveness trial in Myanmar showed that repellent distributed to villages through volunteer networks was associated with a significant reduction of *P. falciparum* infections [16]. Furthermore, distribution of long-lasting insecticidal hammocks “mimicking its implementation in operational conditions” to villages was also found to reduce malaria prevalence in a community-based trial in Viet Nam [17]. However, the effectiveness of the distribution of a package of personal protective interventions specifically targeting high-risk MMPs is yet to be quantified. In order to develop and evaluate the effectiveness of a personal protection package tailored to forest-going MMPs distributed by malaria volunteers, a stepped-wedge cluster-randomised controlled trial will be conducted in Cambodia and Lao PDR. Furthermore, a nested mixed-methods study will be conducted alongside the trial to determine the MMPs’ knowledge, attitude and practice regarding malaria prevention, the acceptability, feasibility and cost-effectiveness of the MMP-tailored malaria prevention tool package—essential outcomes for policy adoption of a new tool or strategy [18]—to maximize translation of findings.

## Methods

This study has three components—an open stepped-wedge cluster-randomised controlled trial to evaluate the effectiveness of personal protection package in reducing the prevalence of *Plasmodium* spp. infection in forest-going MMPs and individuals in their residing villages; a mixed-methods study to explore the acceptability of a personal protection package, feasibility of implementing a personal protection package as a vector control intervention, and knowledge, attitude and practice of MMPs regarding malaria prevention; and cost-analysis to determine the cost-effectiveness of implementing a personal protection package. The main text of this paper focuses on the trial with other study components and data collection tools detailed in Additional file 1.

### Intervention

The intervention in the trial is a personal protection package to be used by the forest-going MMPs for prevention of *Plasmodium* spp. infection. The package was designed in consultation with relevant implementing partners: National Malaria Programmes: Cambodia National Center for Parasitology Entomology and Malaria Control and Laos Center of Malariology Parasitology and Entomology; and non-governmental organizations: Health Poverty Action (HPA), PEDA and CHIAs in Cambodia and Lao PDR.

The intervention package includes three items—WHO pre-qualified long-lasting insecticidal hammock net (LLIHN) (high-density polyester monofilament yarn blended with 2% (w/w) permethrin), two insect repellent bottles (1-piperidinecarboxylic acid 2-(2-hydroxyethyl)-1-methylpropylester, also known as Icaridin), and an MMP-tailored health communication pamphlet. In addition to the pamphlet, behavioural change communication will also be delivered in the forms of health communication sessions in groups and health communication posters posted at or around the MMP’s workplaces. The intervention package will be distributed through the malaria volunteers operated by implementing partners.

### Outcomes

The primary outcome of this trial is the prevalence of *Plasmodium* spp. infection diagnosed by rapid diagnostic test (RDT). Secondary outcomes of this trial include symptomatic malaria infection diagnosed by RDT, *Plasmodium* spp. infection as determined by polymerase chain reaction (PCR), *Plasmodium* spp. infections with drug resistance mutations, prevalence and levels of antibodies to *Plasmodium* spp. and mosquito salivary antigens (Table 1).

**Table 1 Tab1:** Outcome measures of the trial

Outcome measures		Measurement method	Time frame
*Primary outcome measure*			
1A	*Plasmodium* spp. infection diagnosed by RDT [Change in the prevalence of *Plasmodium* spp. infections detected by RDT per week per village]	RDT	Assessed weekly, longitudinally over 12 months
*Secondary outcome measures*			
2A	Symptomatic malaria diagnosed by RDT [Change in the prevalence of symptomatic *Plasmodium* spp. infections detected by RDT per week per village]	RDT and Malaria register	Assessed weekly, longitudinally over 12 months
2B	*Plasmodium* spp. infection as determined by polymerase chain reaction (PCR) [Change in the prevalence of *Plasmodium* spp. infection as determined by PCR from RDT cassette samples and dried blood spot (DBS) samples]	PCR	Assessed weekly, longitudinally over 12 months
2C	*Plasmodium* spp. infections with drug resistance mutations [Change in the prevalence of *Plasmodium* spp. infection with drug resistance mutations]	PCR	Assessed weekly, longitudinally over 12 months
2D	Prevalence of antibodies to *Plasmodium* spp. [Prevalence of antibodies to *Plasmodium* spp. determined by Enzyme Linked Immunosorbent assay (ELISA) from RDT and DBS samples]	ELISA	Assessed weekly, longitudinally over 12 months
2E	Levels of antibodies to *Plasmodium* spp. [Levels of antibodies to *Plasmodium* spp. determined by Enzyme Linked Immunosorbent assay (ELISA) from RDT and DBS samples]	ELISA	Assessed weekly, longitudinally over 12 months
2F	Prevalence of antibodies to vector salivary antigens [Levels of antibody biomarkers of vector exposure]	ELISA	Assessed weekly, longitudinally over 12 months
2G	Levels of antibodies to vector salivary antigens [Levels of antibody biomarkers of vector exposure]	ELISA	Assessed weekly, longitudinally over 12 months

### Outcome collection plan

Data required to determine the primary outcome of the study, *Plasmodium* spp. infection diagnosed by RDT, and secondary outcome 2A (Table 1) will be recorded by malaria volunteers in their routine malaria case register, which is a standardized form developed and used by the implementing partners. When an individual presents to a malaria volunteer for a RDT for malaria, they will be asked to provide another two drops of blood onto a piece of filter paper. Blood spots will be collected on filter papers from all consented individuals immediately before they have received the RDT test from the malaria volunteer.

Used RDT cassettes and dried blood spots will be kept and stored where possible to extract DNA and antibodies to determine secondary outcomes 2B, 2C, 2D, 2E, 2F, and 2G using PCR and ELISA methods as previously described [16, 19–21].

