## Discussion

Targeting residual malaria in high risk areas and populations in the GMS will be critical to achieve regional elimination goals [7]. This study will provide quantitative and qualitative evidence, using a rigorous design and methodology, to evaluate whether a malaria personal protection package (repellent, hammocks and behaviour change communication) can reduce residual malaria transmission among forest-going MMPs in Cambodia and Lao PDR. The intervention package was developed in collaboration with implementing partners and national malaria programs from both Cambodia and Lao PDR. The study will measure implementation research outcomes essential for policy adoption of a new tool or strategy [18]—effectiveness of the intervention package, cost-effectiveness, acceptability, and feasibility—to maximise translation and adoption of findings into National Malaria Guidelines of GMS countries in order to meet national and regional malaria elimination goals.

A strength of the study is that it is a pragmatic randomised trial undertaken in the “real world” and with usual care (distribution through malaria volunteers) and therefore will provide evidence to support whether to deliver personal protection packages to MMPs through established malaria volunteer networks as part of national malaria programs. We considered our trial design against the nine domains of the PRECIS-2 (PRagmatic-Explanatory Continuum Indicator Summary tool version 2) [22] to assess whether our trial design matched “real world” scenarios. All MMPs are *eligible* to receive the intervention and are to be *recruited* in the same manner if this intervention was adopted as part of malaria services provided by malaria volunteers. The study *setting* of the trial and the *organisation* and *flexibility* of intervention delivery in the trial through malaria volunteers is similar to the usual care setting. The intensity of *follow-up* has the potential to be greater than what would be observed during usual care as malaria volunteers have testing targets to meet to ensure that high study power is achieved. The *primary outcome* of RDT detectable *Plasmodium* spp. infection is the detection method used in routine malaria testing so will be of high relevance to normal malaria control practice. The *primary analysis* will be intention-to-treat and all data will be used for primary outcome analysis regardless of village data completeness across time or level of intervention fidelity.

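### The primary outcome is labelled prevalence but measures RDT positivity among people tested, so a change in testing that starts at a village's own switch would bias the odds ratio

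*Protocol article*

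**What the plan says.** - Outcomes: "The primary outcome of this trial is the prevalence of" RDT-detected infection. Table 1 gives the measure as "Change in the prevalence of *Plasmodium* spp. infections detected by RDT per week per village". The opening of Methods frames the aim as lower prevalence among forest-going migrants and the residents of their villages.
- Outcome collection plan: the data "will be recorded by malaria volunteers in their routine malaria case register". A person enters the data "When an individual presents to a malaria volunteer for a RDT for malaria". The article describes no survey, sampling frame or population denominator.
- Intervention: "The intervention package will be distributed through the malaria volunteers operated by implementing partners". In addition, "behavioural change communication will also be delivered in the forms of health communication sessions in groups", with posters at or near workplaces.
- Discussion: follow-up may be more intense than in usual care because "malaria volunteers have testing targets to meet to ensure that high study power is achieved".
- Data analysis: a binomial GLMM with a logit link, fixed terms for intervention status and time, and crossed random effects for village and time. The Discussion relies on adjustment for time to deal with confounding.

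**The concern.** The binomial denominator is the number of RDTs done, not a sample of the village or of its migrants. The label and the data source therefore describe different quantities, and the article's conclusions about prevalence and transmission rest on the label.

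The switch to intervention brings new contact with the volunteer and health communication about malaria. Either could change who comes for a test, or how many come, from that month on. The volunteer who tests and records also delivers the package. The article has no blinding statement, and its word open may mean an open cohort, but a person who hands out hammock nets and repellent cannot be blind to doing so.

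A binomial model reads any shift in the mix of tested people as a shift in infection. The PCR and antibody outcomes use samples from the same tested people, so they share the denominator and offer no independent check.

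**Working it through.** **Inputs from the article (Study design and sample; Study power).** 488 villages; 10 blocks of 44 and one of 48; about 11 RDTs per village-month; 12 months; 1% positivity; target OR 0.66; village ICC 0.42; 5% significance; 90% power.

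**The article's own figures.** 488 × 11 × 12 = 64,416 tests, exactly as stated. A Hussey-Hughes calculation on the proportion scale (12 monthly periods, ICC 0.42, two-sided 5% assumed) gives 90.3% power. The power statement is not the fault here.

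**Positivity at the target effect.** Baseline odds are 0.01/0.99 = 0.010101. Multiplied by 0.66 this is 0.0066667, so p1 = 0.0066667/1.0066667 = 0.0066225, against p0 = 0.01.

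**Change in testing that mimics the target with no change in infection.** Let f be the relative rise in tests after the switch and q the positivity among the added tests. Both are assumptions; the article gives neither. Observed positivity is (p0 + f·q)/(1 + f). Setting this equal to p1 gives f = (p0 − p1)/(p1 − q), with p0 − p1 = 0.0033775. The ratio of case counts after to before is 1 + f·q/p0.

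| q | f | Tests per village-month | Case-count ratio |
|---|---|---|---|
| 0% | 0.0033775/0.0066225 = 51% | 16.6 | 1.00 |
| 0.1% | 0.0033775/0.0056225 = 60% | 17.6 | 1.06 |
| 0.25% | 0.0033775/0.0041225 = 82% | 20.0 | 1.20 |
| 0.5% | 0.0033775/0.0016225 = 208% | 33.9 | 2.04 |

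In every row the odds ratio is 0.66 while case counts are level or rising. A real effect with steady testing would lower both.

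**A smaller change.** For a 25% rise in tests (11 to 13.75 per village-month):
- q = 0: 0.01/1.25 = 0.0080, OR 0.80.
- q = 0.25%: 0.010625/1.25 = 0.0085, OR 0.85.
- q = 0.5%: 0.01125/1.25 = 0.0090, OR 0.90.
- q = 1%: positivity is unchanged, OR 1.00, no bias.
- q = 2% (added testers at higher risk): 0.015/1.25 = 0.012, OR (0.012/0.988)/0.010101 = 1.20.

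**Fewer negative tests.** If the true OR is 0.66 and 34% of tests, all negative, are lost after the switch, positivity is 0.0066225/0.66 = 0.01003 and the OR is about 1.00. The real effect disappears.

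**Chance of a false claim of benefit.** This uses a within-village Poisson approximation over 12 periods, with the probability taken as Φ(|log OR|/SE − 1.96). It assumes no effect on infection and the same change in testing in every village from its switch. A 25% rise gives about 37% (q = 0) or 23% (q = 0.25%); a 50% rise gives 84% or 58%. The nominal rate in that tail is 2.5%.

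**What the model removes.** The time terms absorb changes in testing common to all villages in a calendar month. The village effect absorbs stable differences between villages. A change that begins in each village at its own switch coincides with the intervention indicator, and neither term absorbs it.

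**The case against.** The article states its data source openly, and the Discussion presents routine RDT detection as a deliberate pragmatic choice. It reports no change in testing at the switch. The communication is tailored to migrants and the posters are placed around their workplaces, so the people prompted to test may well be at higher risk, which would hide an effect rather than create one. If added testers have the base 1% positivity there is no bias. Mimicking the whole target effect takes at least half as many tests again. Supporting models of test volume or case counts may sit in an analysis plan that is not shown, and their absence from an article is no fault.

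Most of this stands. It rules out any claim that bias will occur or that it favours the package. It does not repair the mismatch between label and data, nor the fact that the stated model cannot tell fewer infections from a changed mix of testers at the switch.

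Two stronger readings are tempting. A reader might infer that testing targets drive the bias. The article does not say that targets differ between control and intervention periods; common targets act through calendar time, which the model adjusts for, and may even steady test volume. A reader might also infer that targets cannot secure power because extra tests are negative. That follows only if they are all negative; extra tests at the assumed 1% bring proportionally more positives and more information.

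**Conclusion.** The point holds in a limited form. The primary outcome is RDT positivity among people tested, not prevalence in migrants or villages, and the planned analysis leaves it open to bias from any testing change tied to the switch. Size and direction are unknown. At 1% positivity, a 25% rise in tests gives an OR between 0.80 and 0.90 for added tests 0% to 0.5% positive; the full 0.66 needs rises of 51% to 208% over the same range. Higher-risk added testers, or fewer negative tests, push the other way. These figures rest on assumed values of f and q, and the article supports none in particular. That volunteers know the village's state is inferred from their delivering the package. This is a cheap improvement that should be made, not a defect that invalidates the design.

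**What to change.** 1. Name the primary outcome RDT positivity among those tested, and limit claims about prevalence or transmission accordingly.
2. Pre-specify a model of RDTs done per village-month on intervention state, with the same time and village terms as the primary model.
3. Pre-specify a supporting Poisson or negative binomial mixed model of RDT-positive cases per village-month. Use a population offset where current figures exist and rely on village effects otherwise: populations behind the 2018–2020 incidence screen would be dated and nearly constant within a village. Read it together with item 2, because extra testing pushes counts up and positivity down. Counts also depend on testing effort, so agreement between the two models should not be a condition for concluding effectiveness.
4. Add a sensitivity analysis restricted to symptomatic presenters, using the symptom status that outcome 2A already needs. Do not adjust the primary model for symptoms, which are recorded after the switch and may be affected by the package.
5. State that testing targets are the same before and after the switch.

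If the analysis plan already contains items 2 to 4, a cross-reference is enough. The cost is a few extra models on register data and a more modest outcome label. A swap of higher-risk for lower-risk testers at constant volume would still escape items 2 and 3; item 4 is only a partial guard against it.

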### Study setting and population

Villages and worksites in malaria endemic areas of Cambodia (Preah Vihear, Stung Treng and Ratanakiri Provinces) and Lao PDR (Attapeu, Cahmpasack, Khammouane, Saravanh and Savannakhet provinces) will be included in this trial (Fig. 1). The participants will be forest-going MMPs [11] including—traditional slash-and-burn and paddy field farming communities, seasonal agricultural laborers, forest workers in the informal sector, transient or mobile camp residents associated with commercial projects (road/pipeline construction, large-scale logging, etc.), and formal and informal cross-border migrant workers.

